### Study population

This observational study was designed to be broadly inclusive to reflect the need to collect information on pregnant and postpartum women of all ages, with and without chronic medical conditions, and with singleton or multiple gestations. The study will include postpartum women whether or not they choose to breastfeed. The exclusion criteria are limited to behavioral or cognitive impairment, psychiatric disease or any condition that might pose a health risk and interfere with the individual’s ability to participate and/or the evaluation of study objectives (Table 3).

**Table 3 Tab3:** Study Inclusion and Exclusion Criteria

**Inclusion Criteria**	Pregnant Women 1. Pregnant individuals scheduled to receive or have received complete vaccination series of any licensed or EUA COVID-19 vaccine^a^ 2. Willing and able to provide consent for study participation for herself and for her infant prior to initiation of any study procedures.
	Postpartum Women 3. Individuals scheduled to receive or who have initiated vaccination series of any licensed or EUA COVID-19 vaccine within the first 2 months postpartum^b^ 4. Willing and able to provide consent for study participation for herself and for her infant prior to initiation of any study procedures (a separate consent form will be used for their infants).
	All participants 5. Understands and agrees to comply with all study procedures. 6. Agrees to sign medical release for herself and her infant to allow study staff to gather pertinent medical information, pregnancy outcome data, and medical information as needed.
**Exclusion Criteria**	1. Behavioral^c^ or cognitive impairment or psychiatric disease that, in the opinion of the investigator, may interfere with the participant’s ability to participate in the study. 2. Any condition which, in the opinion of the investigators, may pose a health risk to the participant or interferes with the evaluation of the study objectives

*Abbreviations*: *EUA* Emergency Use Authorization

^a^No limitation on age of mother, health status, or gestational age at enrollment

^b^No limitation on maternal age or health status

^c^Includes having a history of alcohol or drug abuse within 1 year prior to study enrollment

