**Fig. 1 Fig1:**
[figure not shown]
Sample Size Calculation based on Width of 95% Confidence Intervals for Neutralizing Antibodies for COVID-19 Vaccines included in MOMI-Vax. Legend: The curve shows neutralizing antibody from Phase 1 studies and demonstrates the inflection point for sample size at approximately 150 individuals per group, with little gain in precision with higher samples sizes. Results similar using binding antibody data (results not shown)

The analysis groups are:Group 1: Individuals who receive a COVID-19 vaccine during pregnancy (up to 200 individuals per vaccine type).Group 2: Individuals who receive a COVID-19 vaccine postpartum (up to 65 individuals per vaccine type).Group 3: Infants of individuals who receive COVID-19 vaccine during pregnancy (approximately 200 infants per vaccine type).Group 4: Infants of individuals who receive COVID-19 vaccine postpartum (approximately 65 infants per vaccine type).Group 5: Individuals who receive additional COVID-19 vaccine(s) (booster) during pregnancy (up to 200 individuals).Group 6: Infants of individuals who received additional COVID-19 vaccine(s) (booster) during pregnancy (approximately 200 infants).

The study will not randomize participants between vaccines, and statistical analyses will seek to adjust for covariates when deemed appropriate to account for potential confounders. All analyses will be done by vaccine type and/or platform or vaccination regimen on all available data, and analyses for each endpoint are outlined in Table 5. Multiple imputation may be used if there is substantial missingness. Additional analysis details will be included in a statistical analysis plan.

**Table 5 Tab5:** Primary, Secondary and Exploratory Objectives, Endpoints and Analyses

	Objectives	Endpoints	Analyses
**Primary**	1. Immunogenicity: To describe kinetics and durability of maternal serum antibodies following receipt of COVID-19 vaccine in individuals vaccinated during pregnancy, by vaccine type and platform.	• Geometric Mean Titer (GMT) of serum immunoglobulin G (IgG) enzyme-linked immunosorbent assay (ELISA) and neutralizing (Neut) antibodies after vaccination and up to 12 months after delivery, by vaccine type and platform^a^	• Geometric Mean Titers (GMTs) and 95% Confidence Intervals (CIs) will be calculated in Group 1. Plots such as reverse cumulative distributions or longitudinal presentations of GMTs will be presented.

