	3. Immunogenicity: To assess the effect of gestational age at vaccination (trimester of gestation), maternal age, health and risk status, on immune responses and durability of antibodies in individuals who receive different COVID-19 vaccines during pregnancy or post-partum, by vaccine type and platform.	• GMT of serum IgG ELISA and Neut antibodies after vaccination in pregnancy by gestational age at vaccination (trimester of gestation) and interval between vaccination and delivery, by vaccine type and platform. GMT of serum IgG ELISA and Neut antibodies after vaccination in pregnancy or postpartum by maternal age, health status, and risk status (e.g., occupation, priority vaccination group) overall and by vaccine type and platform.	• GMTs and 95% CIs will be calculated for Group 1 by strata. Student’s t-tests and linear regression (controlling for potential confounders) will be used to compare strata.
	4. Immunogenicity: To describe the transplacental antibody transfer of SARS-CoV-2 antibodies among individuals vaccinated during pregnancy, by gestational age at vaccination, by interval from vaccination to delivery and maternal age, health and risk status, overall and by vaccine type and platform.	• GMT and ratio of cord blood to maternal serum IgG ELISA and Neut antibodies at delivery by gestational age at vaccination (trimester of gestation) and interval between vaccination and delivery, overall and by vaccine type and platform. • GMT and ratio of cord blood to maternal serum IgG ELISA and Neut antibodies at delivery by maternal age, health status, and risk status, overall and by vaccine type and platform.	• GMTs and ratios of cord blood to maternal serum and 95% CIs will be presented for Group 1 by strata. Student’s t-tests and linear regression (controlling for potential confounders) will be used to compare strata.
	5. Immunogenicity: To describe the kinetics of SARS-CoV-2 antibodies in breast milk of mothers who received vaccine during pregnancy or postpartum, overall and by vaccine type and platform.	• GMT of IgG and immunoglobulin A (IgA) ELISA and Neut antibodies in breast milk at approximately 2 weeks, and 2, 6, and 12 months postpartum, in individuals vaccinated during pregnancy or postpartum, overall and by vaccine type and platform.	• GMTs and 95% CIs will be calculated in Group 1. Plots such as reverse cumulative distributions or longitudinal presentations of GMTs will be presented.

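### Table 5 names Student's t-test for strata whose sizes are not controlled; if strata differ in both size and spread, its error rate moves away from 5%, and Welch's test avoids this cheaply

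*Protocol article*

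**What the plan says.** Table 5 of the protocol article (Statistics section) gives the analysis for secondary objectives 3 and 4. For objective 3 it says "GMTs and 95% CIs will be calculated for Group 1 by strata", and then "Student’s t-tests and linear regression (controlling for potential confounders) will be used to compare strata". Objective 4 repeats the second sentence for cord-to-maternal ratios. The factors in objective 3 are given as "To assess the effect of gestational age at vaccination (trimester of gestation), maternal age, health and risk status, on immune responses"; objective 4 adds the interval from vaccination to delivery.

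Group 1 is defined as "Individuals who receive a COVID-19 vaccine during pregnancy (up to 200 individuals per vaccine type"). The Study population section describes the cohort as covering "pregnant and postpartum women of all ages, with and without chronic medical conditions, and with singleton or multiple gestations". The footnote to Table 3 for pregnant women reads "No limitation on age of mother, health status, or gestational age at enrollment". Under Enrollment, recruitment closes by vaccine type and study group; no stratum quota is mentioned.

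The article gives no stratum sizes, cut-points for age or health status, titer SDs by stratum, or significance level for these tests. It also says "Additional analysis details will be included in a statistical analysis plan".

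**The concern.** Student's test estimates one common variance, and the larger stratum dominates that estimate. If the smaller stratum is more variable, the pooled standard error is too small and false positives rise. If it is less variable, the standard error is too large and the test becomes conservative. With equal-sized strata the two errors cancel.

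Strata cut by trimester, age, health status and risk status in an unrestricted cohort will be equal in size only by coincidence. Unequal spread is also plausible. Any chronic condition is admitted, and under Follow-up, women vaccinated before enrollment have serology drawn at any time after vaccination. The mix of such factors can differ between strata.

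At stake are the p-values for whether trimester, age, health or risk status changes antibody response or placental transfer. The Background expects the results to inform policy and personal decisions and offers the design as a template.

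**Working it through.** **No figure to reproduce.** The article states no alpha, power or SD for these comparisons, so the check asks how far the named test can depart from 5%.

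**Inputs**
- From the article: n = 200 per vaccine type (the upper limit for Group 1); Student's t-test; comparison between strata.
- Assumed: two-sided 5% level (in keeping with the 95% intervals); normal log titers; stratum splits n1:n2 from 100:100 to 20:180; SD ratio a = (SD of smaller stratum)/(SD of larger stratum) from 0.67 to 2.

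**Formula.** With the larger stratum's SD set to 1:
- pooled variance: sp² = [(n1 − 1)a² + (n2 − 1)] / (n1 + n2 − 2)
- assumed over true variance of the difference: r² = sp²(1/n1 + 1/n2) / (a²/n1 + 1/n2)
- large-sample type I error = 2[1 − Φ(1.96 r)]

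**Worked case, 20:180, a = 2**
- sp² = (19 × 4 + 179)/198 = 1.288
- assumed variance = 1.288 × (1/20 + 1/180) = 0.0715
- true variance = 4/20 + 1/180 = 0.2056
- r² = 0.348, r = 0.590, 1.96r = 1.156; type I error = 24.8%

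**Worked case, 50:150, a = 1.5**
- sp² = (49 × 2.25 + 149)/198 = 1.309
- r² = (1.309 × 0.02667)/(0.045 + 0.00667) = 0.676, r = 0.822; type I error = 10.7%

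**Type I error of Student's test, total n = 200 (formula; simulation of 40,000 data sets per cell in parentheses)**

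| Split | a = 0.67 | a = 1.25 | a = 1.5 | a = 2 |
|---|---|---|---|---|
| 100:100 | 5.0% (4.9%) | 5.0% (5.1%) | 5.0% (4.9%) | 5.0% (5.0%) |
| 67:133 | 2.6% (2.7%) | 6.8% (6.5%) | 8.5% (8.5%) | 10.9% (11.2%) |
| 50:150 | 1.7% (1.8%) | 7.9% (7.8%) | 10.7% (10.5%) | 15.1% (15.0%) |
| 40:160 | 1.3% (1.3%) | 8.6% (8.5%) | 12.2% (12.2%) | 18.0% (17.6%) |
| 20:180 | 0.7% (0.8%) | 10.1% (10.0%) | 15.5% (15.7%) | 24.8% (24.8%) |

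Welch's test gave 4.7% to 5.2% in every cell of this table.

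**Sample size does not cure it.** Writing p = n1/n and q = n2/n, r² is close to (pa² + q)/(qa² + p), which does not involve n. For 20:180 and a = 2 this is 1.3/3.7 = 0.351, against 0.348 above. Pooling vaccine types for an overall analysis leaves the problem unchanged at the same split and SD ratio.

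**Regression.** Ordinary least squares with its usual standard errors makes the same equal-variance assumption. Simulation with one covariate and a true null, 20,000 runs per cell:

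| Split, a | Usual SE | HC3 SE |
|---|---|---|
| 20:180, 0.67 | 0.8% | 5.2% |
| 20:180, 1.5 | 15.1% | 5.4% |
| 20:180, 2 | 24.2% | 5.8% |
| 40:160, 1.5 | 12.3% | 5.3% |
| 40:160, 2 | 17.8% | 5.0% |

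**The case against.** The strongest reply is that neither condition for the problem is in the article. It gives no stratum size, and the absence of a quota is not evidence of a 20:180 split; trimester or age strata could be nearly balanced. It gives no SD by stratum. GMTs imply the log scale, where a twofold SD ratio is a fourfold variance ratio. This stands: splits and SD ratios are assumptions, and the upper corner of the table should not be read as a forecast.

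A reader might infer that the strata are known to be very unequal, or that any difference in spread drives the error rate to several times 5% or to near zero. The article does not support the first, and the arithmetic refutes the second. Reaching 15% takes roughly a 1:3 split with twice the SD, or 1:9 with 1.5 times. At 1.25 times the range is about 7% to 10%, and equal strata keep 5%.

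It can also be said that Student's may be generic shorthand in a condensed article, and that the variance option belongs in the SAP. This stands only in part. Table 5 names a test, and the article defers additional details to the SAP, so the choice is stated and not merely left open. The standard errors for the regression are different: the article does not fix them, so robust errors are a suggestion that the SAP could already meet.

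Finally, the primary analyses are descriptive, and no sample size or decision rule in the article rests on these tests. That is right and limits the weight of the point.

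**Conclusion.** The point holds conditionally. The named test, read in its standard form, keeps its 5% level only if strata are about equal in size or in spread, and nothing in the article secures either. For splits of 1:2 to 1:9 out of 200 women, the departure is moderate at modest differences in spread and reaches about 25% only at the far corner (20:180, twice the SD). If the smaller stratum is the less variable one, the loss is in power instead. These sizes rest on assumed splits, assumed SD ratios, normal log titers and a two-sided 5% level.

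This is a cheap improvement to secondary comparisons, not a flaw in the study's main results.

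**What to change.** In Table 5, secondary objectives 3 and 4, replace Student's t-tests with Welch's unequal-variance t-test on log titers and log cord-to-maternal ratios. Preferably also state, in Table 5 or the SAP, that the accompanying linear regressions use heteroscedasticity-consistent (HC3) standard errors. If the SAP already specifies these, aligning the wording of Table 5 is enough.

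The cost is a few words, with no new data or visits. If variances are in fact equal, and the comparison has about 80% power, Welch's test gives up about 1 percentage point of power or less at splits up to 40:160 and about 3 points at 20:180.

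### Secondary 3 and 4 compare gestational age at vaccination by trimester, although weeks are derivable; a continuous, flexible term in the planned regression would retain more information

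*Protocol article*

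**What the plan says.** In the protocol article, Statistics, Table 5, the endpoints of Secondary objectives 3 and 4 look at antibody titers (and, in objective 4, cord-to-maternal ratios) "by gestational age at vaccination (trimester of gestation) and interval between vaccination and delivery". The word trimester is attached to gestational age only. The interval to delivery carries no categories. A further endpoint looks at titers "by maternal age, health status, and risk status (e.g., occupation, priority vaccination group"), again without cut points.

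The analysis column for objective 3 reads "GMTs and 95% CIs will be calculated for Group 1 by strata". Both objectives then close with the same sentence, which names Student's t-tests together with "linear regression (controlling for potential confounders) will be used to compare strata". The regression is therefore in the plan, but its stated purpose is the same as that of the t-tests.

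On the data: the Follow-up section has vaccination dates recorded at routine visits, and the Study outcomes section lists gestational age among the neonatal assessments. Group 1 is defined as "Individuals who receive a COVID-19 vaccine during pregnancy (up to 200 individuals per vaccine type"), and women may enrol in any trimester.

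**The concern.** How response and transplacental transfer depend on the timing of vaccination is the question these two objectives ask. Comparing trimesters treats a woman vaccinated at 14 weeks like one vaccinated at 27 weeks, and separates women at 27 and 28 weeks. Any gradient within a trimester is lost, and the result is a step function that depends on where the cuts fall.

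A two-sample t-test also fits a three-level factor poorly. Each test sets one trimester aside, and three tests are needed for each antibody and vaccine type. A regression on trimester indicators uses all the women, so that part of the problem belongs to the t-tests alone, but the regression still loses what lies inside each trimester. If a real gradient exists, a finding of no difference between trimesters becomes more likely than it need be.

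**Working it through.** **Are weeks available?** Gestational age at vaccination equals gestational age at birth minus the time from vaccination to birth. Each component is recorded or follows from recorded dates. Assigning a trimester needs the same calculation.

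**The plan's own sizing figure.** The legend of Fig. 1 "demonstrates the inflection point for sample size at approximately 150 individuals per group". It concerns the width of the confidence interval for a GMT. The SD behind it is not given and the figure is not shown, so it can be neither reproduced nor refuted. Going from 150 to 200 changes the width by the factor √(150/200) = 0.866, whatever the SD. The figure says nothing about power for Secondary 3 or 4.

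**Inputs.** From the document: n = 200 (the ceiling per vaccine type) and three trimesters. Assumed: two-sided 5% level, cuts at 14 and 28 weeks, vaccination between weeks 2 and 38, timing either uniform or with trimester shares 15/40/45% (uniform within trimester), residual SD 1, effect 0.20 SD of log titer per SD of the effect shape, and no covariates.

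**Formula for the regression codings.** R² = 0.20²/(1 + 0.20²) = 0.04/1.04 = 0.0385. If a coding captures a share k of the effect's variance, the noncentrality is λ = n·kR²/(1 − kR²). Power follows from the noncentral F with 1 df (line) or 2 df (3-knot spline, or three trimesters). For example, trimesters under uniform timing keep k = 0.883 of a linear effect: kR² = 0.0340 and λ = 200 × 0.0340/0.9660 = 7.0.

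| Effect | Coding | k, uniform / 15-40-45 | λ | Power |
|---|---|---|---|---|
| Linear | line, 1 df | 1.000 / 1.000 | 8.0 / 8.0 | 80.4% / 80.4% |
| Linear | spline, 2 df | 1.000 / 1.000 | 8.0 / 8.0 | 71.1% / 71.1% |
| Linear | trimesters, 2 df | 0.883 / 0.866 | 7.0 / 6.9 | 65.0% / 64.1% |
| U-shaped, centred at 20 weeks | line, 1 df | 0.000 / 0.135 | 0 / 1.0 | 5.0% / 17.4% |
| U-shaped | spline, 2 df | 0.989 / 0.975 | 7.9 / 7.8 | 70.5% / 69.8% |
| U-shaped | trimesters, 2 df | 0.568 / 0.609 | 4.5 / 4.8 | 45.1% / 48.0% |

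**Pairwise t-tests, linear effect.** The trimester means are 8, 21 and 33 weeks.
- Uniform timing: the SD of weeks is 36/√12 = 10.39 and the group sizes are about 67, 78 and 56. First against third: difference 0.20 × (33 − 8)/10.39 = 0.481, standard error about √(1/67 + 1/56) = 0.18, power 75%.
- 15/40/45% timing: SD 9.5, sizes 30, 80 and 90. Difference 0.20 × 25/9.5 = 0.526, standard error about √(1/30 + 1/90) = 0.21, power 69–70%.
- Adjacent trimesters: 24–37% over both timings.

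**Agreement.** Separate runs of the same scenarios gave 80–81% (line), 71–73% (spline), 64–66% (trimesters), 69–75% (first against third) and 24–36% (adjacent) for the linear effect. For the U shape they gave 68–69% (spline), 45–47% (trimesters) and 5–17% (line). The two sets differ by at most about 2 points.

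**The case against.** The case on the other side has five parts.

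- **Regression is already planned.** A reader might infer that the plan relies on t-tests alone. It does not: the same sentence includes a confounder-adjusted regression. The sound contrast is grouped against continuous, not t-test against regression.
- **The gain is modest if the effect is linear.** A reader might take the distance from the straight line to the trimester test, about 15 points, as the gain. That benchmark has 1 df, whereas a safe recommendation needs a flexible term with 2 df, as many as the trimester test. The gain is then about 7 points. Under uniform timing, a t-test of first against third trimester (75%) does at least as well as the spline's overall test. This objection stands.
- **Maternal age and interval.** A reader might infer that these are cut into groups as well, with larger losses. The article states no cuts for either, and the shared wording about strata also covers truly categorical factors such as occupation. No loss can be claimed.
- **Coding belongs in the SAP.** The article defers further detail to an SAP that is not shown, and cut points or functional form would normally go there. For gestational age, however, Table 5 already names the trimester grouping, the methods and their purpose. That is a stated choice.
- **The study is descriptive.** It was sized on interval width, and the article does not say that a non-significant trimester test will be read as no effect. This limits the consequence but leaves the cheaper and better analysis available.

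**Conclusion.** The concern holds for gestational age at vaccination. Table 5 commits both the t-tests and the regression to a trimester comparison when weeks can be had at no data cost. Under the stated assumptions, a 3-knot spline beats the three-level comparison in all four scenarios: by about 7 points of power if the effect is linear, and by a little over 20 points if it is U-shaped. A single straight line would do better still for a linear effect but almost fails for a U shape, so the case is for a flexible continuous term and not for any continuous term.

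These sizes depend on an assumed effect, assumed timing and assumed cuts, because the article gives none of them. A reader might infer that the study is too small or a stated number wrong. The document does not support that: Secondary 3 and 4 carry no power target. This is an inexpensive improvement to two secondary analyses.

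**What to change.** In Table 5, Secondary 3 and 4, make the main comparison for gestational age at vaccination the confounder-adjusted linear regression already planned, on log titer and on the log cord-to-maternal ratio. Enter gestational age in weeks as a 3-knot restricted cubic spline, in place of trimester strata and pairwise t-tests. Keep GMTs, ratios and 95% CIs by trimester as descriptive tables.

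Treat maternal age (years) and the interval from vaccination to delivery (days) as continuous in the same way. Fit the interval in a separate model from gestational age at vaccination: the two add up to gestational age at delivery, so they are nearly collinear among births of similar gestation. The t-tests can stay for factors that are categorical by nature.

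The cost is one extra degree of freedom against a straight line, and a fitted curve that is slightly harder to report than a trimester contrast. No new data are needed.

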	6. Immunogenicity: To describe the kinetics and durability of maternal serum antibodies following receipt of COVID-19 vaccine in individuals vaccinated postpartum, by vaccine type and platform.	• Postpartum individuals: GMT of serum IgG ELISA and Neut SARS-CoV-2 antibodies pre- and/or post-vaccination, and at approximately 2, 6, and 12 months after delivery, overall, and by vaccine type and platform.	• GMTs and 95% CIs will be calculated in Group 3. Plots such as reverse cumulative distributions or longitudinal presentations of GMTs will be presented.
	7. Immunogenicity: To describe the kinetics and durability of serum SARS-CoV-2 antibodies in infants of individuals vaccinated postpartum, by vaccine type and platform.	• GMT of serum IgG ELISA and Neut antibodies at approximately 2 and 6 months of age in infants of postpartum individuals, overall and by vaccine type and platform.	• GMTs and 95% CIs will be calculated in Group 4. Plots such as reverse cumulative distributions or longitudinal presentations of GMTs will be presented.
**Exploratory**	1. To describe the effectiveness of COVID-19 vaccines against maternal COVID-19 infection during pregnancy and postpartum.	• Incidence of laboratory confirmed COVID-19 and severity of disease during study participation assessed through passive surveillance in individuals vaccinated during pregnancy or postpartum vs. rates in unvaccinated population of women of childbearing age, overall and by vaccine type and platform.	• Incidence rates and 95% CIs will be calculated in Groups 1 and 3.
	2. To describe the effectiveness of maternal antibodies to provide protection against SARS-CoV-2 infection/symptomatic disease/severity in infants in the first 12 months of life.	• Incidence of laboratory confirmed COVID-19 and severity of disease during study participation assessed through passive surveillance in infants of individuals vaccinated in pregnancy or postpartum vs. background rates in infants of unvaccinated population, overall and by vaccine type and platform.	• Incidence rates and 95% CIs will be calculated in Groups 2 and 4.

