	3. To describe the effectiveness of breast milk antibodies to provide protection against SARS-CoV-2 infection/symptomatic disease/severity in infants in the first 12 months of life.	• Incidence of laboratory confirmed COVID-19 and severity of disease during study participation through passive surveillance in breastfed infants vs. not breastfed infants, by vaccine type and platform. • Incidence of laboratory confirmed COVID-19 and severity of disease during study participation through passive surveillance in breastfed infants of individuals vaccinated during pregnancy vs. postpartum, overall and by vaccine type and platform.	• Incidence rates and 95% CIs will be calculated in Groups 2 and 4.

*Abbreviations*: *GMT* Geometric Mean Titer, *IgG* immunoglobulin G, *ELISA* enzyme-linked immunosorbent assay, *Neut* neutralizing, *IgA* immunoglobulin A

^a^Pregnant individuals: pre- and/or post-vaccination, at delivery, and at approximately 2, 6, and 12 months postpartum

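### Table 5 contradicts the plan's own group definitions: four rows name a wrong analysis group, three more leave out postpartum women, and no row assigns an antibody analysis to them

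*Protocol article*

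**What the plan says.** The list of analysis groups in the Statistics section (after the Fig. 1 legend) sets four populations, apart from the later booster groups:

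- "Group 1: Individuals who receive a COVID-19 vaccine during pregnancy (up to 200 individuals per vaccine type")
- "Group 2: Individuals who receive a COVID-19 vaccine postpartum (up to 65 individuals per vaccine type")
- "Group 3: Infants of individuals who receive COVID-19 vaccine during pregnancy (approximately 200 infants per vaccine type")
- "Group 4: Infants of individuals who receive COVID-19 vaccine postpartum (approximately 65 infants per vaccine type")

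The same section refers the reader to Table 5 for the analysis of each endpoint and leaves further detail to a statistical analysis plan.

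In the Analyses column of Table 5:

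- Secondary 6 (serum antibodies of women vaccinated postpartum): "GMTs and 95% CIs will be calculated in Group 3". The same sentence stands in Primary 3, where infants are meant and it is correct.
- Exploratory 1 (maternal COVID-19): "Incidence rates and 95% CIs will be calculated in Groups 1 and 3".
- Exploratory 2 and Exploratory 3 (infant COVID-19): "Incidence rates and 95% CIs will be calculated in Groups 2 and 4".
- Secondary 5 (breast milk of women vaccinated in pregnancy or postpartum): "GMTs and 95% CIs will be calculated in Group 1". Secondary 2 and Secondary 3 likewise name Group 1 only.

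**The concern.** Table 5 is the only place in the article that ties each endpoint to an analysis population. If the group numbers there do not match the definitions, an analyst who follows them takes the wrong people for some endpoints and leaves out the right people for others.

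The postpartum cohort is the most exposed. These women are followed with repeated blood sampling and optional breast milk collection, yet no row directs an antibody analysis to them. Infants of women vaccinated in pregnancy are also exposed: they are the natural subjects of an objective on protection by maternal antibodies, but the rows on infant COVID-19 leave them out. The article also offers itself as a template for other studies, so the error could be copied.

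**Working it through.** There is no planned figure to reproduce. The check compares, row by row, the population in the objective and endpoint columns with the group in the Analyses column, using the definitions of Groups 1 to 4.

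| Row | Population in objective and endpoint | Groups needed | Groups named | Result |
|---|---|---|---|---|
| Primary 1 | Women vaccinated in pregnancy | 1 | 1 | consistent |
| Primary 2 | Same, cord-to-maternal ratio | 1 | 1 | consistent |
| Primary 3 | Infants of women vaccinated in pregnancy | 3 | 3 | consistent |
| Secondary 1 | All women and infants | 1–4 | 1–4 | consistent |
| Secondary 2 | Women, both cohorts | 1, 2 | 1 | omits 2 |
| Secondary 3 | First endpoint: pregnancy only. Second: both cohorts | 1; then 1, 2 | 1 | second endpoint omits 2 |
| Secondary 4 | Women vaccinated in pregnancy | 1 | 1 | consistent |
| Secondary 5 | Breast milk, both cohorts | 1, 2 | 1 | omits 2 |
| Secondary 6 | Women vaccinated postpartum | 2 | 3 | wrong group |
| Secondary 7 | Infants of women vaccinated postpartum | 4 | 4 | consistent |
| Exploratory 1 | Women, both cohorts | 1, 2 | 1, 3 | adds 3, omits 2 |
| Exploratory 2 | Infants, both cohorts | 3, 4 | 2, 4 | adds 2, omits 3 |
| Exploratory 3 | Infants, both cohorts | 3, 4 | 2, 4 | adds 2, omits 3 |

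**Count.** The table has 3 + 7 + 3 = 13 rows. Four name a group outside the stated population (Secondary 6, Exploratory 1, 2 and 3), three omit Group 2 (Secondary 2, 3 and 5), and six are consistent: 4 + 3 + 6 = 13.

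**Where Group 2 appears.** Only in Secondary 1, correctly, and in Exploratory 2 and 3, wrongly. Rows that assign serum or breast-milk titres to Group 2: 0.

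**Infants left out of Exploratory 2 and 3, per vaccine type.** Planned infants are 200 + 65 = 265. Group 3 contributes 200, so 200/265 = 75% are not covered. The second endpoint of Exploratory 3 contrasts breastfed infants by whether the mother was vaccinated in pregnancy or postpartum. Without Group 3 the first arm of that contrast is empty.

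**Women left out of Exploratory 1, per vaccine type.** 65 of 200 + 65 = 265, or 65/265 = 25%.

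**Could one relabelling repair the table?** All 24 orderings of the four populations over the labels 1 to 4 were tried. The best swaps labels 2 and 3. That makes Secondary 6 and Exploratory 1, 2 and 3 correct, but it makes Primary 3 wrong and leaves the three omissions, so 4 of 13 rows still fail. Two numbering schemes therefore appear to be mixed, and each row has to be settled separately.

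**The case against.** The strongest reply is that these are labelling slips that a reader can see through. Each of the four contradictory rows states its population in the neighbouring columns, and the swap of labels 2 and 3 shows a likely source. All three primary rows are correct. The affected rows are secondary or exploratory, most are descriptive, and data collection is unaffected. This stands, and it lowers the severity. It does not make the table correct. Deferring detail to an analysis plan does not help either, because the defect is a contradiction in what is stated and not a missing detail.

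Three stronger readings are tempting and are not supported:

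- That all seven rows name the wrong group. Only four do. In Secondary 2, 3 and 5, Group 1 is right but incomplete, and the first endpoint of Secondary 3 properly belongs to Group 1 alone.
- That the exploratory rates would be averages over mothers and infants, half of them the wrong people. The article does not say that the named groups are pooled; one rate per group is an equally natural reading. Equal headcounts would not give equal person-time anyway, since follow-up is up to 20 months for pregnant women and 12 months for infants.
- That the Secondary 6 endpoint would be computed in nobody. The row points to Group 3 infants. What can be said is that it points to no postpartum woman.

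**Conclusion.** The point holds. Four of 13 rows contradict the definitions and three more omit Group 2. The consequences, if the table is followed, are that the postpartum women have no assigned serum or breast-milk antibody analysis, that about 200 of 265 planned infants per vaccine type are outside Exploratory 2 and 3, and that one comparison in Exploratory 3 cannot be done.

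The headcounts are planned numbers that the article gives as approximate or as upper limits. The conclusion assumes that the listed definitions, and not some other numbering, are the intended ones; Primary 3 and Secondary 1, 4 and 7 agree with them. An analysis plan that is not shown may already use the right groups. Whether Group 2 was left out of Secondary 2, 3 and 5 by design cannot be told from the article.

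Severity: should be fixed. No primary row is affected, and the intended populations can be recovered from the objectives.

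**What to change.** Correct the Analyses column of Table 5:

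- Secondary 6: Group 2.
- Exploratory 1: Groups 1 and 2.
- Exploratory 2 and 3: Groups 3 and 4.
- Secondary 2, Secondary 5, and the endpoint of Secondary 3 on maternal age, health and risk status: Groups 1 and 2. The gestational-age endpoint of Secondary 3 stays in Group 1.

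With these changes all 13 rows agree with the definitions of Groups 1 to 4. If Group 2 was left out of Secondary 2, 3 or 5 on purpose, narrow the objective and endpoint wording instead. Carry the same assignments into the statistical analysis plan. The cost is wording only; no new data, samples or participants are needed.
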